##### Think cool

In this module, participants learn cognitive emotion regulation strategies. The module is based on the Think Cool Chain, and consists of a cognitive approach to emotion regulation that is typically used in current interventions (e.g., [39, 40]). The first step of the chain (session 1) is to signal anger, with an anger thermometer that is based on situations, feelings, sensations and cognitions (e.g., “they always blame me”). Adolescents also learn to identify the “tipping” point, the point on the thermometer where it is smart to use one of the emotion regulation strategies. The second step of the chain is to practice three cognitive emotion regulation strategies (cognitive distraction, cognitive relaxation and cognitive reappraisal). Adolescents practice with these strategies in session 1 and 2. The third step of the chain is cognitive problem solving, which is practiced stepwise in session 3, 4, and 5. Adolescents learn specific cognitive problem-solving skills (understand a problem from multiple perspectives, think about possible solutions and possible consequences of these solutions, decide which is the most suitable solution) and practice these skills in a stepwise manner with paper-and-pencil exercises.

##### Act cool

In this module, participants learn behavioral emotion regulation strategies with the Act Cool Chain, consisting of a behavioral approach to emotion regulation that is typically used in current interventions (e.g., [40, 41]). The first step (session 1), is to signal anger with an anger thermometer, similar to the thermometer that is used in the Think Cool module. However, in the Act Cool module the thermometer is based on behaviors (e.g., “if I become angry I raise my voice”) rather than cognitions. The second step of the chain is to practice behavioral emotion regulation strategies (behavioral distraction, behavioral relaxation and time out). Adolescents practice these strategies in session 1 and 2. The third step of the chain is behavioral problem solving, which is practiced with behavioral exercises in session 3, 4, and 5. Adolescents learn specific behavioral skills (set a boundary, ask for help, ask for an explanation) and practice with difficult situations (accusations, disappointments, frustration).

##### Clinician training and supervision

Clinicians providing the experimental training receive a two-day training course, guided by the developers of the training manual. The training course starts with an introduction providing information regarding the theoretical background of the modules and practical tips with regard to the implementation of the modules. On the first training day, the focus is on the Think Cool module whereas the second training day focuses on the Act Cool module. In the afternoon session, clinicians practice their training skills by participating in and reflecting on role-plays. Moreover, the training course focuses on differentiation between cognitive and behavioral approaches, creating a safe atmosphere, motivating adolescents, explaining exercises, and discussing at-home assignments. During the intervention period, clinicians participate in at least two 3-h supervision sessions in which clinicians bring in topics that they would like to discuss or practice, and reflect on their skills. In addition, clinicians are able to receive consultation by phone on request.

#### Control condition

Participants in the control condition will receive care-as-usual (CAU). CAU is defined as the standard care that is available at school for all adolescents with behavior problems. This includes, for example, behavior management techniques provided by teachers (e.g., reinforcing positive behavior). Moreover, participants in both conditions are not withheld to receive other kind of help, if necessary (e.g., psychopharmaca). The received CAU and additional help will be measured and reported.

### Measures

All constructs, measures and informants are summarized in Table 2.

**Table 2 Tab2:** Overview of measures and informants

Variable	Concept	Measure	Informant
Eligibility screening	Externalizing behavior	TRF	Teacher
	Autism Spectrum Problems	ASV	Teacher
	Intelligence	WISC-III-NL	Adolescent
Primary outcomes	Emotion regulation difficulties	DERS	Adolescent
	Emotion regulation strategies	FEEL-KJ, Vignette	Adolescent
	Externalizing behavior	YSR, TRF, CBCL	Adolescent, teacher, parent
	Weekly primary outcomes	Weekly questionnaire	Adolescent
Secondary outcomes	Mood variability	Daily Diary	Adolescent
	Internalizing problems	YSR	Adolescent
Mediators	Emotion regulation difficulties	DERS	Adolescent
	Emotion regulation strategies	FEEL-KJ, Vignette	Adolescent
	Social information processing	SIVT	Adolescent
Moderators	Affective reactivity	ARI-S	Adolescent
	Parental acceptance-rejection	PARQ	Parent
	Intelligence	WISC-III-NL	Adolescent
	Treatment integrity	TIQ, audiotapes	Clinician
Other variables	Demographics	Questions	Adolescent, parent
	Received care	Questions	School psychologist

*Note. TRF* Teacher Report Form, *ASV* Autisme Spectrum Vragenlijst, *YSR* Youth Self Report, *CBCL* Child Behavior Checklist, *DERS* Difficulties in Emotion Regulation Scale, *FEEL-KJ* Fragensbogen zur Erhebung der Emotionsregulation bei Kinder und Jugendlichen, *SIVT* Sociale Informatie Verwerkings Test, *ARI-S* Affective Reactivity Index, *PARQ* Parental Acceptance-Rejection Questionnaire, *TIQ* Treatment Integrity Questions

#### Screening measures

##### Externalizing behavior problems

Teachers will report on the externalizing behavior problems of the adolescent with the externalizing subscale of the Teacher Report Form age 6–18 [42]. This scale consists of 32 items (e.g., “Fights a lot”) that are rated on a 3-point scale from 0 *(not true)* to 2 *(very true or often true).*

##### Severity of autism spectrum symptoms

The severity of autism spectrum symptoms will be measured with the teacher reported *Autisme Spectrum Vragenlijst* [43]. This questionnaire consists of 24 items (e.g., “Exhibits odd, repetitive behaviors”) on a 5-point scale from 1 *(totally not agree)* to 5 *(totally agree).*

##### Intelligence

Intelligence will be assessed with the Dutch version of the Wechsler Intelligence Scale for Children (WISC-III-NL) [44, 45]. If the WISC-III-NL was completed by the adolescent within 24 months before the start of the study, this total IQ score will be used. If this score is not available, the subtests “Block Design” and “Vocabulary” will be completed by the adolescent. Subsequently, global intelligence will be estimated, based on the sum of the scaled subtest scores, with the formula for approximation of Full Scale IQ (FIQ) [46]. FIQ estimates are found to be reliable and strongly correlated with the total IQ score [47, 48].

#### Primary outcome measures

##### Emotion regulation difficulties

The Dutch version of the brief Difficulties in Emotion Regulation Scale (DERS) will be used to measure emotion regulation problems [49, 50]. The DERS is a 15-item self-report measure that assesses difficulties in emotion regulation. The items (e.g., “When I am upset, I become out of control”) are rated on a 5-point scale from 1 *(almost never)* to 5 *(almost always).*

##### Emotion regulation strategies

Emotion regulation strategies in response to feelings of anger will be assessed with the Dutch version of the Fragensbogen zur Erhebung der Emotionsregulation bei Kinder und Jugendlichen (FEEL-KJ) [51]. The subscale anger is assessed in this study and consists of 30 items (e.g., “If I feel angry… I do something fun”) that are rated on a 5-point scale from 1 *(never)* to 5 *(almost always).* The questionnaire distinguishes adaptive and maladaptive emotion regulation strategies.

In addition, cognitive and behavioral emotion regulation strategies will be measured with a newly developed vignette measure. The measure is based on earlier vignette measures [12, 52]*.* The adolescent reads a vignette that is meant to elicit feelings of anger, and rates how likely it is that he/she will use a specific emotion regulation strategy, on a 7-point scale from 0 *(definitely not)* to 6 *(definitely).* Per vignette, there are six behavioral strategies (adaptive strategies: relaxation, behavioral distraction, social support; maladaptive strategies: direct expression, indirect expression, avoidance), and six cognitive strategies (adaptive strategies: cognitive reappraisal, cognitive distraction, putting into perspective; maladaptive strategies: self-blame, rumination, suppression).

##### Externalizing behavior

Externalizing behavior will be measured from a multi-informant perspective, with subscales of the ASEBA-questionnaires that are administered to adolescents, their teachers, and parents [42]. Adolescents (YSR), Teachers (TRF), and Parents (CBCL) will complete respectively the 32, 32, and 35 items of the externalizing scale of the Dutch ASEBA versions [53]. Items (e.g., “Fights a lot / I fight a lot”) are rated on a 3-point scale from 0 *(not true)* to 2 *(very true or often true).*

##### Weekly measure

Emotion regulation and aggression will also be assessed with a 6-item self-reported weekly measure. The questionnaire contains three items for emotion regulation (e.g., “how often this week did you become *so* angry, that you could not control yourself?”) and 3 items for aggression (e.g., “How often did you hit someone this week?”) that are rated on a 5-point scale from 0 *(never)* to 4 *(more often, … times).* The measure is based on items of the DERS and YSR [42, 49].

#### Secondary outcome measures

##### Mood variability

Mood variability will be measured with the Daily Mood Device, an adapted version of the Electronic Mood Device [54, 55]. In the current study, the mood variability measure is integrated in the weekly measure smartphone application. At each measurement moment, adolescents are asked to rate the intensity of their daily mood for happiness, sadness, anger, and anxiety (“Today I feel …”) on five consecutive days. Each mood state will be measured with three items (12 items in total), that are rated on 9-point scale from 1 *(not happy / angry / …*) to 9 *(happy / angry / …)*. The words that are used for happiness are “glad”, “happy”, and “cheerful”, for sadness: “sad”, “down”, and “dreary”, for anger: “angry”, “cross”, and “short-tempered”, and for anxiety: “afraid”, “anxious”, and “worried”.

##### Internalizing problems

Internalizing problems will be reported by the adolescents with the internalizing scale of the Youth Self Report age 11–18 [42]. This subscale consists of 34 items (e.g., “I cry a lot”) that are rated on a 3-point scale from 0 *(not true)* to 2 *(very true or often true).*

#### Potential mediators

Emotion regulation skills (see for measures the primary outcome section) and social information processes are viewed as protentional mediators for models in which the effects of the Think Cool Act Cool training on externalizing behavior problems are tested.

##### Social information processing

Social information processing skills biases and deficits will be assessed with the *Sociale Informatie Verwerkings Test* (SIVT) [56]. The SIVT consists of six videos that show hostile, ambiguous or accidental interpersonal problems, involving a peer or adult perpetrator. In all videos, the outcome of the situation is negative for the victim. Different steps of social information processing (encoding, interpretation, goal setting, response generation, response evaluation and selection) are measured with a semi-structured interview and multiple-choice questions. In the current study, only ambiguous and accidental situations will be used because earlier research shows that with hostile situations, aggressive and non-aggressive are not very well distinguishable [57]. At each time point, the adolescent will view two videos; an ambiguous and an accidental situation with both a peer and adult perpetrator, but the order will be counterbalanced.

#### Potential moderators

##### Affective reactivity

Reactivity will be assessed with the Affective Reactivity Index (ARI-S) [58]. The ARI-S is a 6-item self-report measure that assesses irritability (e.g., “I often lose my temper”) on a 3-point scale from 0 *(not true)* to 2 *(certainly true).*

##### Parental acceptance-rejection

Parental acceptance-rejection will be measured with 18-items of the short version Parental Acceptance-Rejection Questionnaire (PARQ) [59]. Parents will report on three subscale of the PARQ; warmth, neglect and undifferentiated rejection (e.g., “I say nice things about my child”). Items are rated on a 4-point scale from 1 *(almost never true)* to 4 *(almost always true).*

##### Treatment integrity

Treatment integrity is conceptualized in this study as the extent to which the intervention is implemented as intended [60]. To measure treatment integrity, clinicians will fill in a questionnaire after each session. The questionnaire is based on other measures of treatment integrity [60–62] and consists of several domains; treatment exposure, treatment adherence, and treatment differentiation (e.g., “It was difficult to focus on behavior rather than cognitions in this session”). The questionnaire also measures participant comprehension and responsiveness (e.g., “The adolescent participated actively in this session”). In total, the measure consists of approximately 25 items, depending on the content of the session. Items are answered on 4-point scale from 1 *(not at all)* to 4 *(totally).* Moreover, all training sessions will be audiotaped. A random selection of 10% of the sessions will be scored on different aspects of treatment integrity (e.g., adherence, differentiation) by independent coders.

#### Other information

Demographic information (gender, ethnicity and socioeconomic status) will be assessed at baseline. In addition, the received care-as-usual and additional help will be measured at T3.

### Analyses

Data will be analyzed according to the intention-to-treat principle [63], with multiple imputation as technique to handle missing data. To answer the first research question, whether the Think Cool Act Cool emotion regulation training is effective in enhancing emotion regulation skills and decreasing externalizing behavior problems, data of T1-T3 will be analyzed with analysis of variance and/or structural equation modeling. We will examine whether different aspects of emotion regulation and multi-informant perspectives of externalizing behaviors problems can be combined into latent variables. If this is the case, these latent variables will be used, in structural equation models. Otherwise, the analyses of variance will be conducted separately for the different constructs. To examine which module (Think Cool versus Act Cool) and which sequence most effectively increases emotion regulation capacities, we will use piecewise growth curve analyses and analysis of variance. Moderation will be tested by using multi-group analyses or regression analyses, and mediation will be tested with random-intercept cross-lagged panel models and parallel-process piecewise latent growth curve modeling. The analyses and reporting of results will be carried out according to the Consolidated Standards of Reporting Trials (CONSORT) [64].

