### Sample size

The sample size of this study is based on the expected difference on the primary outcome variables (emotion regulation and externalizing behavior problems) between the intervention condition (both sequences together) and the control condition. Meta-analyses demonstrated that the expected effect size (*d*) of cognitive behavioral therapy for children and adolescents with externalizing behavior problems is between 0.25 and 0.30 [5, 6]. To detect a small to medium effect (Cohen’s *d* = 0.25–0.30), with a two-sided type I error rate of 0.05, a power of 0.95, and three measurement moments, we will need between 100 and 142 participants [36]. To account for dropout, we have determined the total sample size to be 160 (80 participants in the control condition and 80 participants in the intervention condition).

Because previous research did not investigate differences between cognitive and behavioral training modules, it is not possible to estimate the expected effect size for the difference between modules. However, a sensitivity-power analyses showed that with 80 participants in the two intervention arms, an error rate of 0.05, a power of 0.95, and 19 repeated weekly measurements, even small effect sizes of 0.09 can be demonstrated with within-subjects analyses [36].

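### The main effectiveness analysis names ANOVA and/or SEM on T1-T3 but no baseline-adjusted contrast; making T3 adjusted for T1 the primary test would recover some power at almost no cost

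*Protocol article*

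**What the plan says.** The Analyses section addresses the first research question, effectiveness against care-as-usual, by stating that "data of T1-T3 will be analyzed with analysis of variance and/or structural equation modeling". It then sets an order for the two methods, depending on whether a latent-variable model proves feasible for these measures: "If this is the case, these latent variables will be used, in structural equation models. Otherwise, the analyses of variance will be conducted separately". ANOVA is therefore the fallback. The section does not say which ANOVA term is the test, whether T1 enters as an outcome or a covariate, or which time point is primary.

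The Sample size section bases the trial on the difference "between the intervention condition (both sequences together) and the control condition", takes an expected d that "is between 0.25 and 0.30", and concludes that with "a power of 0.95, and three measurement moments, we will need between 100 and 142 participants". The total is then set at 160 (80 per condition) to allow for dropout.

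Procedure and randomization places T1 before training in both conditions and randomises individuals to intervention or control.

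**The concern.** Because individuals are randomised and T1 is taken before training, the expected group difference at T1 is zero. T1 holds no information on the treatment effect as an outcome, but much as a covariate. A T1-T3 ANOVA with T1 as an outcome wave offers two tests of the group effect, and neither is the direct question:

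- The group main effect averages the three waves, so the effect is diluted by a wave at which it must be zero.
- The group-by-time test spreads its power over 2 degrees of freedom, covering any pattern of divergence, and rests on within-person change. A change score has variance 2(1-rho) against 1-rho² for a baseline-adjusted outcome. At rho = 0.5 that is 1.00 against 0.75, so the adjusted variance is 25% smaller.

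Power is at stake, and so is whether the trial ends with a single intervention-control effect and confidence interval that answers its first question.

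**Working it through.** **Inputs from the protocol article.** d = 0.25-0.30, two-sided alpha 0.05, power 0.95, three measurements, 100-142 participants before dropout, 160 in total, 80:80 (all Sample size).

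**Assumptions not in the document.** Compound symmetry with correlation rho between waves; zero T1 difference; the stated d is the effect at T3; at T2 the effect is either half (linear build-up) or already full; all 160 participants contribute fully.

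**Step 1: the plan's own figure.** For a repeated-measures ANOVA group main effect with m = 3 waves, lambda = f²·N·m / (1 + (m-1)·rho). With rho = 0.5:

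- f = 0.25, N = 142: lambda = 0.0625 × 142 × 3 / 2 = 13.31, power 0.952.
- f = 0.30, N = 100: lambda = 0.09 × 100 × 3 / 2 = 13.50, power 0.953.

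Two fewer participants at either end falls below 0.95, so both ends match exactly. The match needs the stated d to be entered as Cohen's f. With f = d/2 the same test needs 558 and 388. The group-by-time test with f = d/2 gives 168 and 116 at rho = 0.5, and comes close (144 and 100) only at rho of about 0.57. The main-effect match suggests that T1 was treated as an outcome wave in the sizing; it does not prove it.

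**Step 2: three tests at N = 160, d = 0.30, rho = 0.5.**

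- *Group main effect.* SE = √[(4/N)·(1+2·rho)/3] = √(0.025 × 0.6667) = 0.129. The mean effect over waves is d/2 = 0.15 (linear) or 2d/3 = 0.20 (full from T2). Noncentrality 1.16 or 1.55; power 0.211 or 0.337.
- *Group-by-time, 2 df.* f² = d²/24 (linear) or d²/18 (full from T2); lambda = 3·N·f² / (1-rho). Linear: 480 × 0.00375 / 0.5 = 3.6, power 0.375. Full: 480 × 0.005 / 0.5 = 4.8, power 0.483.
- *T3 adjusted for T1.* SE = √[4(1-rho²)/N] = √(4 × 0.75 / 160) = 0.137. Noncentrality 0.30/0.137 = 2.19; power 0.586.

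A simulation of 20,000 trials at these settings gave 0.214 / 0.338, 0.374 / 0.485 and 0.579, all within one point of the formulas.

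**Step 3: the range (N = 160; paired values are linear / full from T2).**

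| rho | d | Main effect | Group-by-time | T3 adjusted for T1 |
|---|---|---|---|---|
| 0.3 | 0.25 | 0.190 / 0.300 | 0.204 / 0.260 | 0.377 |
| 0.3 | 0.30 | 0.252 / 0.406 | 0.278 / 0.359 | 0.507 |
| 0.5 | 0.25 | 0.161 / 0.250 | 0.271 / 0.350 | 0.442 |
| 0.5 | 0.30 | 0.211 / 0.337 | 0.375 / 0.483 | 0.586 |
| 0.7 | 0.25 | 0.142 / 0.216 | 0.427 / 0.545 | 0.595 |
| 0.7 | 0.30 | 0.184 / 0.290 | 0.580 / 0.713 | 0.752 |
| 0.8 | 0.25 | 0.135 / 0.203 | 0.598 / 0.732 | 0.745 |
| 0.8 | 0.30 | 0.173 / 0.272 | 0.767 / 0.880 | 0.882 |

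Gain from adjustment at rho = 0.5: 9-21 points over group-by-time (0.442 - 0.350 to 0.586 - 0.375) and 19-38 over the main effect (0.442 - 0.250 to 0.586 - 0.211). Over rho 0.3-0.8: about 0-23 points over group-by-time (0.882 - 0.880 to 0.507 - 0.278) and about 8-71 over the main effect (0.377 - 0.300 to 0.882 - 0.173). The adjusted contrast is at least as powerful in every row.

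At N = 142, d = 0.30 and rho = 0.5 the picture is the same: 0.193 / 0.305, 0.337 / 0.435 and 0.536.

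**The case against.** The strongest reply is that the plan does not commit to the inefficient test. SEM comes first and ANOVA is the fallback; the article does not say how T1 enters either one, and an SEM on T1-T3 could well adjust for it. Such detail may sit in an analysis plan that is not shown. The Background section also speaks of examining changes from baseline to post-intervention, which points to group-by-time rather than the diluted main effect, and against group-by-time the gain can be negligible.

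Much of this stands. A reader might infer from the section that the main test simply is a T1-T3 ANOVA, or from the exact match in the sample size that the main effect averaging in T1 will be tested. The document supports neither: the tested term is not stated, and a sizing formula does not fix the analysis. Nor can one unconditional figure be given for the loss, since it depends on rho, the effect pattern and the term tested. At rho 0.7-0.8 with the full effect from T2, the loss against group-by-time is only 0-5 points. No power was computed for the latent-variable route.

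What does not stand is that this is only missing detail. ANOVA on the three waves is a stated route to the main result, and a better method is available from data already being collected.

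**Conclusion.** The point holds as an improvement to the planned method, not as an error in it. With N = 160, d = 0.25-0.30 and an assumed rho of 0.5, power is 16-34% for the main effect, 27-48% for group-by-time and 44-59% for T3 adjusted for T1. The direction was constant over rho 0.3-0.8; the size was not. These figures rest on compound symmetry, no T1 difference and complete data, and they apply to the ANOVA route.

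A reader might also infer that adjustment repairs the trial's power. It does not: even at rho = 0.8 the adjusted test reaches 75-88%. The gap to 0.95 comes from the sample-size calculation, whose N matches d entered as f, and has to be dealt with separately.

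**What to change.** In the Analyses section, name as primary test for the first research question the pooled intervention-control difference at T3, adjusted for T1 of the same measure. In the ANOVA route this is an ANCOVA; in the SEM route, enter T1 as a covariate or constrain it equal across conditions. Report the difference with a confidence interval, and the T2 difference as secondary. A T1-T3 ANOVA can remain as description.

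The cost is a change of wording and one covariate degree of freedom, with no new data, visits or participants. Adjustment for school and wave is not part of this change: as a fixed factor it would cost one degree of freedom per additional cluster, and the figures above do not include it.
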